### 11.5.3 Secondary Analysis

Fleiss’ kappa will be estimated to assess interrater reliability between 6 readers. Specificity, accuracy, positive predictive value, and negative predictive value will be calculated for FDCT.

For the subset of patients with an isolated infratentorial hemorrhage the sensitivity of FDCT for its detection including its 95%-CI will be reported separately.

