# 3. BACKGROUND AND RATIONALE

## 3.1 Background and Rationale for the clinical investigation

Despite concerted efforts, stroke is still one of the leading causes of mortality and disability worldwide.^26-28^ Stroke can be divided into two main types: ischemic and hemorrhagic stroke. In severely affected patients, which will most likely be disabled or dead after the stroke - if not timely treated - roughly 80% of the strokes are caused by a vessel occlusion (i.e., ischemic strokes) and 20% are due to an intracranial bleeding (i.e., hemorrhagic stroke).

For acute ischemic stroke (AIS) patients due to a vessel occlusion, mechanical thrombectomy (MT) has substantially reduced the burden of disease. However, still roughly 50% of all AIS patients due to a large vessel occlusion (LVO are severely disabled after the stroke or die within 90 days after the stroke.^7, 8^ Since all neuroprotective trials so far have failed to show any beneficial effect in such patients^33, 34^, patient triage is an important area of inquiry due to the high time-dependency of the efficacy of MT.^9^ On average one minute delay in time to treatment causes the irreversible loss of 1.9 million neurons, 14 billion synapses and 12 km of myelinated fibers.^35^ Especially the door to puncture time is an independent variable for patient outcome as was shown in an analysis of 6,756 AIS patients with an LVO. Among every 1,000 patients treated, every 15-minute decrease in door-to-puncture time was associated with 21 (95%-CI 8 – 34) more patients discharged to home, 18 (95%-CI 4 – 31) more patients having freedom from disability and 22 (95%-CI 7 – 37) more patients having functional independence at discharge. It was further associated with 15 (95%-CI 4 – 26) fewer in-hospital deaths or patients being discharged to a hospice.^24^ These results were further validated by other study groups.^9, 22, 23^ Reducing time-delays in AIS patients has also important implications on a socioeconomic level as was recently shown by Kunz et al. They concluded based on the data of 7 large randomized controlled trials (RCTs) that every 10 minutes of earlier treatment result in an average gain of 39 days (95% prediction interval 23 – 53) of disability free life, translating to a reduction of $10,915 (95% prediction interval $5,928 - $15,365) of life-time healthcare costs.^29^

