However, the widespread implementation of this direct to angiography workflow has been impended by the difficulty of differentiating between ischemic and hemorrhagic stroke with FDCT.^39, 40^ As it is not possible to differentiate between ischemic and hemorrhagic stroke without brain imaging, it is of pivotal importance that hemorrhage exclusion can be performed safely and reliably with native FDCT imaging as well. A missed intracranial hemorrhage, i.e. an hemorrhagic stroke (which make up between 15 and 20% of all severely affected stroke patients according to an analysis of the Swiss Stroke Registry) could have potentially dramatical (and lethal) consequences due to different treatment strategies.^41^ Up till now this was only evaluated in retrospective studies, which showed very high sensitivity and specificity in the detection of intracranial hemorrhage with the last generation of FDCT.^6, 18^ However, prospective high-quality studies with large patient cohorts on this topic are still missing. We further did not find any ongoing studies on clinicaltrials.gov or within the WHO trial registry.

Therefore, we aim with this study to investigate if non-contrast syngo DynaCT Sine Spin imaging is non-inferior to non-contrast MDCT imaging regarding its sensitivity and specificity for the detection of intracranial hemorrhages. Non-contrast syngo DynaCT Sine Spin imaging will be deemed non-inferior if the lower bound of the 95%-confidence interval (95%-CI) of the sensitivity is above 95% and the lower bound of the 95%-CI of the specificity is above 95% (pre-defined non-inferiority margin). If non-inferiority could be established, this would guarantee for a safe triage of stroke patients. We are confident, that if our study shows non-inferiority of non-contrast syngo DynaCT Sine Spin imaging it will pave the way for the widespread implementation of the above described direct to angiography workflow, allowing more AIS patients to live a self-sustained, independent life after their stroke. Due to the high burden of disease any measurement of improvement is of high need. Conversely if our study fails to establish non-inferiority of non-contrast syngo DynaCT Sine Spin imaging for the detection of intracranial hemorrhage, it might prevent patients from undergoing harmful treatments.

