### 3.4.2 Clinical evidence to Date

We screened 4,950 records, out of which one evaluated non-contrast syngo DynaCT Sine Spin for the detection of intracranial haemorrhage.^6^ Furthermore, we found a few publications evaluating non-contrast cranial FDCT imaging in general for bleeding detection.^18, 42, 43^ The two most recent publications found very high sensitivities for the detection of intraparenchymal or intraventricular haemorrhage (97-100%) but only moderate to high sensitivity for the detection of subarachnoid haemorrhages, especially in the posterior fossa.^6, 42^

However, all these studies had important methodical issues. Most importantly, only a minority of patients came from the most relevant patient group: suspected stroke patients presenting with a spontaneous intraparenchymal and/or intraventricular haemorrhage. They mainly used surrogate patients, as they included patients which developed an intraparenchymal and/or intraventricular haemorrhage after an intervention. Findings from these patients cannot be generalized to patients presenting with a spontaneous intraparenchymal and/or intraventricular haemorrhage as haemorrhage location, size and distribution might differ substantially. An analysis of the Swiss Stroke Registry of patients from the University Hospital Basel showed that in our targeted patient population (suspected acute stroke patients with an NIHSS ≥7) 16% presented with such a spontaneous haemorrhage. Secondly, the studies did not define the patient population prospectively but rather used all patients available for their analysis. Therefore, the reported sensitivities and specificities could not be generalized to our targeted patient population (patients presenting with symptoms suggestive of a severe acute ischemic stroke or an intracranial bleeding). Third, in some of their cases an FDCT which was done prior to an intervention was compared to an MDCT which was done after the intervention. In these cases, it is not always feasible to deduce, if a bleeding occurred due to the intervention or was missed in the first scan. Also, due to the retrospective nature of the studies selection bias could not be ruled out.

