## 4.3 Secondary Objectives

The secondary Objectives are to determine:

- the positive predictive value of FDCT for the detection of intracranial hemorrhages.
- the negative predictive value of FDCT for the detection of intracranial hemorrhages.
- the interrater agreement of FDCT with regard to the occurrence of intracranial hemorrhage

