It was tested whether the lower end of the 95%-CI did not fall below the prespecified margins. For sensitivity and for specificity this was 95%. The 95%-CI of sensitivity and specificity were calculated by fitting a generalized linear random-effects model with a logit link function. Random-effects variables were patient and reader, outcome variable was the randomly generated binary vector. To converge to model estimates, the algorithm of the “nloptwrap”-optimizer was applied.

From the model, the lower end of the 95%-CI of the fixed-effect intercept was extracted and transformed to percent. The 95%-CI was calculated by the method of Wald. If the lower ends of the 95%-CIs of sensitivity and specificity both did not fall below a pre-defined margin, the experiment was rated as “successful”. The percentage of “successful” experiment out of all experiments characterizes the study power. Each sample size, n_i=1,..,19_ = 80,…,260 was evaluated by sampling 999 times n_i_ individual samples with a range of readers from 1 to 7.

If the total weight of “difficult cases” is set at 0.02, the number of difficult cases at n= 14, the power at 90% the number of readers at 6, and the drop-out rate at 5%, a total of **252 patients** (238 patients without drop-outs) must be recruited. The patients must be pre-selected in a ratio of hemorrhage positive to hemorrhage negative of 1:1, i.e., 126 patients are presenting with and 126 patients without intracranial hemorrhage (out of which 14 present with an isolated infratentorial intracranial bleeding). The number of readers was set based on our model calculations since with a lower number of readers the sample size fluctuated substantially (over 100%). The needed sample size however stabilized at a range of 5 to 7 readers. With this number of readers, the sample size fluctuated only by 10% (with 7 readers being the lowest and with 5 the highest).

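### Section 11.5.3 plans predictive values on a sample with haemorrhage prevalence fixed at 50%, so PPV would be overstated by about 5.5 to 8 points for a target population at 15-20%

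*Protocol*

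**What the plan says.** PPV and NPV are secondary objectives in the synopsis and in protocol section 4.3, which lists "the positive predictive value of FDCT for the detection of intracranial hemorrhages" and the matching negative value. Section 11.5.3 states the method in one sentence: "Specificity, accuracy, positive predictive value, and negative predictive value will be calculated for FDCT". It names no prevalence, formula or weighting. Section 11.6 bases all analysis on the full analysis set.

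The make-up of that set is fixed in advance. Section 6.1 enrols patients into buckets after the non-contrast MDCT has been read. Section 11.2 says "The patients must be pre-selected in a ratio of hemorrhage positive to hemorrhage negative of 1:1", that is, "126 patients are presenting with and 126 patients without intracranial hemorrhage".

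The protocol describes its target population differently. Section 3.4.2 reports that "in our targeted patient population (suspected acute stroke patients with an NIHSS ≥7) 16% presented with such a spontaneous haemorrhage". Section 3.1 gives haemorrhagic strokes, "which make up between 15 and 20% of all severely affected stroke patients according to an analysis of the Swiss Stroke Registry", and elsewhere uses a round 20%.

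The only correction for enrichment is in section 6.1 and in the primary analysis (11.5.2). Isolated infratentorial bleeds are 14 of the 126 haemorrhages (11%) and enter the sensitivity estimate with a fixed weight of 2%. Section 11.5.3 does not say whether that weight carries over to the secondary measures.

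**The concern.** Sensitivity and specificity are conditional on true status, so 1:1 enrolment does not distort them. PPV, NPV and accuracy depend on the proportion with haemorrhage. Calculated directly from this sample, they describe a population in which half of the patients are bleeding. The trial's own figures put that share at about one in five or one in six.

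This matters because the stated use is direct-to-angiography triage, and predictive values are what a clinician would read for that decision. Sections 2 and 3.5 also present the enrolled patients as closely resembling those scanned in practice. For haemorrhage prevalence that cannot be so, and the description invites readers to take a sample PPV at face value.

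**Working it through.** **Sample prevalence.** Section 11.2 gives 238 patients before drop-out, or 119 per group. With 5% drop-out, 119 / 0.95 = 125.3, rounded up to 126 per group and 252 in total. This reproduces the stated figure. Prevalence = 126 / 252 = 50%. The protocol states no PPV or NPV to reproduce.

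**Inputs.** Section 11.2 assumes sensitivity (Se) 99%, specificity (Sp) 98%, and 70% sensitivity for isolated infratentorial bleeds. Taking 99% to apply to the other haemorrhages:
- with the 2% weight: Se = 0.98 × 0.99 + 0.02 × 0.70 = 98.4%
- unweighted, as the cases fall in the sample: Se = (112 × 0.99 + 14 × 0.70) / 126 = 120.68 / 126 = 95.8%

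**Formulas**, with p the prevalence:
- PPV = Se·p / [Se·p + (1 − Sp)(1 − p)]
- NPV = Sp(1 − p) / [Sp(1 − p) + (1 − Se)p]
- Accuracy = Se·p + Sp(1 − p)

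**Example, Se 99%, Sp 98%.** At p = 0.50, PPV = 0.495 / (0.495 + 0.010) = 98.0%. At p = 0.16, PPV = 0.1584 / (0.1584 + 0.0168) = 90.4%.

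**Results (%), Sp 98% throughout:**

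| Se | p | PPV | NPV | Accuracy |
|---|---|---|---|---|
| 99 | 50 | 98.0 | 99.0 | 98.5 |
| 99 | 20 | 92.5 | 99.75 | 98.2 |
| 99 | 16 | 90.4 | 99.8 | 98.2 |
| 99 | 15 | 89.7 | 99.8 | 98.15 |
| 98.4 (weighted) | 50 | 98.0 | 98.4 | 98.2 |
| 98.4 (weighted) | 20 | 92.5 | 99.6 | 98.1 |
| 98.4 (weighted) | 16 | 90.4 | 99.7 | 98.1 |
| 98.4 (weighted) | 15 | 89.7 | 99.7 | 98.1 |
| 95.8 (unweighted) | 50 | 97.95 | 95.9 | 96.9 |

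**Reading the table:**
- **PPV.** The overstatement is 98.0 − 92.5 = 5.5 points at 20% prevalence, 98.0 − 90.4 = 7.6 at 16% and 98.0 − 89.7 = 8.3 at 15%. It hardly depends on which sensitivity is used. False alarms among positive readings are 2.0% in the sample and 9.6% at 16%, about five times as many.
- **NPV.** The understatement at 16% is 99.8 − 99.0 = 0.8 points at Se 99%, and 99.7 − 98.4 = 1.3 points at the weighted Se. If the sample value is unweighted, it is 99.7 − 95.9 = 3.8 points.
- **Accuracy.** With the weight, it moves from 98.2% to 98.1%. Unweighted in the sample it would be 96.9%, which is 1.2 points below the weighted value at 16%.

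**Sensitivity to the assumed reader rates.** Over the rates simulated in section 11.2 (Se 98.5-99.5%, Sp 97.5-98.5%), PPV at 16% is 88.2-92.7%, against 97.5-98.5% at 50%.

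**The case against.** The strongest reply is that section 11.5.3 is silent and does not commit to an error. It names the measures but not the prevalence, and section 11 leaves detailed methodology to a statistical analysis plan that is not at hand. Basing all analysis on the full analysis set does not settle the matter either, because a Bayes calculation would take its sensitivity and specificity from the same set. It stands that the protocol nowhere prescribes crude sample proportions. The plain reading of the text nevertheless gives them. The protocol also treats correction for enrichment as its own business: it reweights an 11% share to 2% in section 6.1 but leaves the larger shift, 50% against 15-20%, uncorrected. A later plan could cure this but should not have to.

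Several limits on size also stand:
- A reader might infer that PPV, NPV and accuracy are all seriously wrong. Only PPV moves materially. The NPV error is towards caution on the protocol's main safety worry, a missed haemorrhage, and accuracy barely changes with the weight applied.
- With Se and Sp both at 95%, PPV would be 95.0% in the sample and 78.4% at 16%. That is a boundary case, not an expected result, because success requires both lower confidence bounds to lie above 95%.
- The 16% comes from one hospital, in patients with NIHSS of 7 or more, and counts intraparenchymal or intraventricular bleeds. The trial also admits subarachnoid haemorrhage, and patients with suspected haemorrhagic stroke without a stated NIHSS threshold. The relevant share may therefore be higher, which would narrow the PPV gap.
- The 1:1 ratio is disclosed, so crude values need not be banned. Clear labelling is enough.

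**Conclusion.** The point holds, and it rests mainly on PPV. Followed as written, section 11.5.3 would give a PPV of about 98.0%, where the protocol's own prevalence range implies about 90% to 92.5%: an overstatement of roughly 5.5 to 8 points. NPV would be understated by about 1 point with the 2% weight, or about 4 points without it, and the text does not say which applies.

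These sizes assume the planned sensitivity and specificity, 70% sensitivity in isolated infratentorial bleeds, and a target prevalence of 15-20%.

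It would be tempting to conclude that the trial's main result is compromised. The documents do not support that. Sensitivity, specificity, the 95% margins and the sample size do not depend on the haemorrhage share in this way, and the predictive values carry no hypothesis or decision rule. This is a secondary-analysis fault that should be corrected before the results are reported.

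**What to change.** In section 11.5.3, state that PPV, NPV and accuracy will be derived by Bayes' rule from the 2%-weighted sensitivity and the specificity over a target prevalence range of 15-20%, including the registry's 16%. Confidence intervals should come from the delta method or a bootstrap. State also that any crude values are specific to the 1:1 enriched sample and are not predictive values for clinical use. A short note should say that the 16% figure is limited to intraparenchymal and intraventricular bleeds.

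The cost is two or three sentences and a little programming. No patients, readings or data are added and the primary analysis does not change. The reported PPV will be lower and the NPV slightly higher.

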11.5.4 Interim Analysis

No interim analysis is planned.

### 11.5.5 Deviation(s) from the original statistical plan

Changes to the statistical analysis plan will be under version control at the Clinical Trial Unit, Department for Clinical Research, University Hospital Basel.

## 11.6 Handling of missing data and drop-outs

The number and proportion of subjects eligible for and compliant with each follow-up examination will be presented. Careful planning and conduct of the study will minimise the occurrence of missing data as far as possible.

All analysis will be based on FAS. Missing data will be described but not imputed. For each patient that withdraws consent before the final outcome assessment, an additional patient is included.

# 12. QUALITY ASSURANCE AND CONTROL

## 12.1 Data handling and record keeping / archiving

### 12.1.1 Case Report Forms (CRF)

For each enrolled trial subject, an eCRF will be maintained. All data will be entered in coded way in the eCRF at the local site. eCRFs must be kept current to reflect subject status at each phase during the course of the trial and are part of the central acquisition by the CTU Basel. Coded identification for each patient will be as follow: [trial-ID]-[site-no]-consecutive number. Authorized to enter data into the eCRF are the local trial team staff according to the authorization list. Authorized persons will be identified by their usernames. The local PI is responsible for proper training and instruction of the trial personnel filling data into the eCRF.

### 12.1.2 Specification of source data and source documents

Source data must be available at the site to document the existence of the trial subjects. The following documents are source documents and can only be found at the local trial site:

- Informed consent form

- Patient screening, enrolment and identification log

- Patient records including reports from treating physician

- Documentation of the patients medical treatment

- Documented worksheets of scores (NIHSS)

- Radiological images from the FDCT and MDCT

- Radiology reports

- Any other relevant record to document AEs and SAEs

### 12.1.3 Archiving of essential clinical investigation documents

All trial data must be archived at the participating site for a minimum of 10 years or according to national requirements after trial termination or premature termination of the clinical trial. In addition, the electronic data will be kept for the mandatory period.

## 12.2 Data management

### 12.2.1 Data Management System

The eCRFs in this trial are implemented electronically using a dedicated electronic data capturing (EDC) system (secuTrial®). The EDC system is activated for the trial only after successfully passing a formal test procedure. All data entered in the eCRFs are stored on a Linux server in a dedicated Oracle database. Responsibility for hosting the EDC system and the database lies with the University Hospital Basel.

### 12.2.2 Data security, access and back-up

The server hosting the EDC system and the database is kept in a locked server-room. Only the system administrators have direct access to the server and back-up tapes. A role concept with personal passwords (site investigator, statistician, monitor, administrator etc.) regulates permission for each user to use the system and database as he/she requires.

All data entered into the eCRFs are transferred to the database using Secure Sockets Layer (SSL) encryption. Each data point has attributes attached to it identifying the user who entered it with the exact time and date. Retrospective alterations of data in the database are recorded in an audit table. Time, table, data field, original value and altered value, and the user are recorded (audit trail).

A multi-level back-up system is implemented.

### 12.2.3 Analysis and archiving

For the final analyses, data files will be extracted from the database after final database closure into statistical packages to be analysed. The status of the database at this time will be recorded in special archive tables. The trial database with all archive tables will be securely stored by the CTU Basel and the University Hospital Basel for at least 10 years. The Sponsor-Investigators will also keep the Trial Master File and interim/final reports for at least 10 years.

### 12.2.4 Electronic and central data validation

Data is checked by the EDC system for completeness and plausibility. Furthermore, selected data points are cross-checked for plausibility with previously entered data for that subject. In addition, central data reviews will be performed on a regular basis to ensure completeness of the data collected and accuracy of the primary outcome data.

Before database lock the local PI will validate the collected data with his signature.

## 12.3 Monitoring

All source data must be accessible for auditing and monitoring. Monitors and auditors will maintain patient confidentiality. All questions from the monitors will be answered during the monitoring.

A risk-based monitoring approach will be implemented for this trial. The risks of the trial will be assessed by the Sponsor-Investigators. A multi-level monitoring plan will be defined based on these risks. It will describe the regular standardized and manual checks of the entered data in the trial database, the remote monitoring activities and the on-site monitoring visits. The Sponsor-Investigators will delegate the monitoring tasks to qualified institutions upon individual agreement.

## 12.4 Audits and Inspections

Authorities have the right to perform inspections, and the University Hospital Basel has the right to perform on-site auditing during working hours upon reasonable prior notice. The auditor/inspector must have access to all medical records, the investigator's trial related files and correspondence, and the informed consent documentation that is relevant for this clinical trial.

PIs will allow the persons responsible for the audit or the inspection to have access to the source data/documents and PIs will answer any questions arising. All involved parties will keep the patient data strictly confidential.

## 12.5 Confidentiality, Data Protection

The information contained in this protocol is copyright protected by the University Hospital Basel. This information is given for the needs of the trial and must not be disclosed to persons outside of the trial community without prior written consent of the University Hospital Basel.

Trial-related data of the patient will be provided in a coded way. The names of the patients will not be disclosed to persons outside of a participating site. A unique patient identification number will be attributed to each patient registered into the trial (for more details see section 12.1.1). Identification of patients must be guaranteed at each site using the patient screening, enrolment and identification list. In order to avoid identification errors, patient’s identification number and the year of birth have to be provided on the eCRF. Patient confidentiality will be maintained according to applicable legislation.

Direct access to source documents will be permitted for purposes of monitoring, audits and inspections. The monitoring institution (i.e., CTU Basel or Semmes Murphey Foundation or another institution authorized by the Sponsor-Investigator) and the local authorities will have access to all information necessary for such tasks during and after the study.

Regarding the data specified in Appendix B (“Specified Data”), University Hospital Basel (the Sponsor) grants Siemens Healthineers a non-exclusive, unrestricted, perpetual, fully paid-up, transferable and sublicensable right to use and/or have used the Specified Data, in any manner whatsoever (in particular to reproduce, distribute, including the right to lease and the right to make available to the public). This grant of rights includes the right of Siemens Healthineers to use the Specified Data in unmodified or modified form, alone or in combination with other data, in all known and unknown ways for the purpose of applying for regulatory approval (i.e. device clearances, registration certification and/or responding to requests of authorities), education, marketing and/or sales of devices and/or services. According to University Hospital Basel`s evaluation the Specified Data contain (amongst others) Personal Data. Siemens Healthineers and its Affiliates will process and disclose Personal Data to third parties only for the following purposes: applying for regulatory approval (i.e. device clearances, registration certification and/or responding to requests of authorities) and/or education. Selected images generated from the specified data can be used for marketing and/or sales of devices and/or services after prior written approval of the University Hospital Basel.

